### **5.5. Treatment protocol**

Take 1 tablet of the drug sublingually each time. Place the drug at the edge of the lingual frenulum, and keep it until there is no obvious foreign body sensation. Avoid chewing or swallowing undisintegrated drugs directly during administration.

The first dose should be administered as soon as possible after randomization; According to the results of human pharmacokinetic study, the plasma concentration has decreased to 1/10 of Cmax 6 hours after administration. The second dose should be not less than 6 hours but not more than 12±1 hours from the first dose. The drug should not be administered more than 2 times a natural day; Each subsequent dose should be taken for 14 consecutive days (28 doses) at an interval of 12 ± 1 h (calculated with the fixed administration time as the baseline point).

Each subject should only take up to 28 doses. If the medication is missed or suspended halfway, the subject should continue to take the drug after 14 days, but not more than 28 doses or 14+3 days. Backup drugs should only be used in the following cases, otherwise they should be uniformly recovered to the Sponsor.

- 1) Loss of drugs;
- 2) Breakage of drugs.

If all 30 tablets are taken, it is inferred from the available toxicological evidence that there will be no significant risks in theory, but such incidents still need to be truthfully recorded.

### **5.6. Treatment adjustment**

No gastrointestinal safety problem was observed during the animal test of Y-2 Sublingual Tablets. Even if the drug is taken by mistake, it will not cause serious consequences, but may weaken the drug effect. Therefore, in the case of medication by mistake, the investigator should still be informed, and this medication will not be repeated.

**5.7. Criteria for discontinuation of treatment or withdrawal**

This Section describes the circumstances under which a subject should be withdrawn from the study prematurely at the discretion of the investigator or the Sponsor. A distinction should be made between the concepts of discontinuation of treatment and withdrawal from the entire study. The procedures (including follow-up) to be performed and the data to be collected in different situations should also be defined. If resumption of treatment is allowed after drug suspension, relevant criteria should be clearly defined. If it is allowed to replace the dropout subjects, the relevant criteria should be clearly described.

**5.7.1. Criteria for discontinuation of or withdrawal from the treatment**

Treatment should be discontinued in the following cases:

1. Intolerable adverse reactions occur during treatment that the investigator concludes that further treatment is not appropriate;
2. Serious violation of the inclusion and exclusion criteria is found after enrollment, and both the investigator and the Sponsor think the treatment needs to be discontinued;
3. New disease changes unrelated to the investigational product occur during treatment that the investigator concludes that further treatment is not appropriate;
4. Interventional therapy (including cerebrovascular stenting) is considered necessary by the investigator during treatment;
5. The subject is unwilling to continue the treatment.

All subjects who have completed the informed consent form and are eligible for enrollment in the trial have the right to withdraw from the clinical trial at any time. The subjects can withdraw from the study if the following conditions are met during the study:

- 1) The subject experiences intolerable adverse reactions;
- 2) The subject asks to withdraw and is unwilling to continue to participate in the study;
- 3) The investigator thinks that the subject cannot complete this study due to poor compliance;
- 4) The subject is lost to follow-up;
- 5) The subject is pregnant;

- 6) The subject participates in other clinical trials;
- 7) The investigator considers that the subject is not appropriate to continue to participate in the study for other reasons.

For withdrawn subjects, the original adverse events will still be followed up, but no other information will be collected, including new adverse events, unless the investigator thinks such events are related to the drug.

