### **5.4.2. Emergency unblinding**

Emergency unblinding is allowed only in the following circumstances: in case of a serious adverse event suspected to be related to the investigational product, the principal investigator of the site should report to the Sponsor to decide whether to initiate the emergency unblinding procedure. Once the emergency unblinding is conducted, the case is

considered dropped out. If the emergency unblinding happens during the treatment period, the medication should be stopped.

This double-blind trial will be invalid if all blind codes are disclosed or the emergency unblinding rate exceeds 20% during the study.

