#### **5.7.2. Handling of discontinuation of or withdrawal from the treatment**

Subjects who have withdrawn during the trial are all considered as dropout cases, and the reasons are shown in Section 5.7.1 "Reasons for withdrawal".

When a subject drops out, the investigator should contact the subject as much as possible to complete the assessment items that can be completed at visit 4 (withdrawal visit). If the subject drops out during the treatment period, the time of the last medication should be recorded. Those who drop out due to adverse reactions also need to be treated as specified in Section 7.3.

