**6.3.2. D90 ( $\pm 7$ ) (visit 5)**

- Vital signs and physical examination (including weight)
- Blood routine, blood biochemistry (Hepatic and renal function, blood glucose (fasting), blood lipids, myocardial enzyme, electrolytes and homocysteine), urine routine, coagulation function and ECG examination
- NIHSS score
- mRS score
- SSS TOAST classification (to be completed during the trail period after enrollment)

Note: For subjects who drop out in the midway, they should try to complete the visit (withdrawal visit) according to the requirements of visit 5.

At sites participating in the research of exploratory indicator biomarkers, a tube of venous blood (about 4mL) should be sampled from the subject before the first administration and on Day 7 ( $\pm 1$ ) (and Day 14 (+3)) after the administration, and send it to the unified

laboratory for testing. See Section 2.2.4 for specific indicators.

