### 6.3.3. Follow-up endpoint

All subjects who have been treated with investigational product need to be followed up until:

1. Visit 5 has been completed according to the proposal;
2. Subjects died during follow-up period;
3. Serious violation of the inclusion and exclusion criteria is found after enrollment, and both the investigator and the Sponsor think the follow-up visit needs to be discontinued;
4. If the subject withdrew from the study midway (see Section 5.7.1 for Reasons for withdrawal), the time of the last evaluation shall be the follow-up endpoint. If the subject withdrew due to intolerable adverse reactions, the follow-up visit shall be carried out according to Section 7.3.

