## 2.6 Randomization and Blinding

All eligible subjects will be randomly assigned to the investigational or control group according to the ratio of 1:1. The random number table is generated by the standardized software. The detailed parameter settings are set by the randomization plan.

In this trial, a centralized competitive enrollment randomization method will be used, and subjects will be assigned a "screening number" after signing the informed consent form and before performing study-related tests. Subject screening numbers must not be reused.

After the subjects passed screening, the investigator or designee obtained the information of randomization number and corresponding drug number through the randomization system, and distributed the corresponding study drugs according to the randomization number and drug number.

Randomization will be stratified by:

- Onset time:  $\leq 24$  hours vs  $> 24$  hours;
- Investigational site.

The color, description, and packaging (including batch number and shelf life) of the investigational drug (Y-2 sublingual tablet) and placebo control drug (Y-2 sublingual tablet placebo) were identical. Blinding process was completed by statisticians unrelated to this clinical trial. After blinding, the blinding codes will be sealed in duplicate and stored in the leading site and the sponsor, respectively.

The trial was unblinded just once. After the last subject completes the 90-day follow-up in the whole trial, after blind verification, the data is locked and unblinding is performed, that is, the corresponding group of each subject is identified. For interim analysis, according to IDMC charter, unblinded data will be reviewed centrally by IDMC members and their statistical analysis will be performed by a third party unblinded statistician independent of the study project team to ensure blinding during the conduct of the trial.

When a serious adverse event suspected to be related to the investigational drug occurs during the trial, the principal investigator at the site should report to the sponsor to decide whether to initiate the emergency unblinding procedure. Once the blind was broken emergently, the case was treated as a dropout and medication was stopped if the blind was broken emergently during treatment.

This double-blind trial was invalidated if the total blind codes were leaked or emergency unblinding exceeded 20% during the study.

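### Withdrawn patients have no clear Day-90 mRS requirement, their new AEs are kept only if judged drug-related, and follow-up after emergency unblinding is undefined

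*Combined protocol and SAP*

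**What the plan says.** Protocol 5.7 sets out to separate stopping treatment from leaving the study and to define the data collected in each case. Section 5.7.1 gives two lists. Intolerable adverse reactions appear in both. The withdrawal list adds grounds that rest on judgement: "The investigator thinks that the subject cannot complete this study due to poor compliance" and "The investigator considers that the subject is not appropriate to continue to participate in the study for other reasons". For withdrawn subjects, existing AEs are followed, "but no other information will be collected, including new adverse events, unless the investigator thinks such events are related to the drug". Under 6.3.3 the last evaluation becomes their follow-up endpoint. The same section lets follow-up end after a serious eligibility violation if "both the investigator and the Sponsor think the follow-up visit needs to be discontinued".

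Emergency unblinding is allowed only for an SAE suspected to be drug-related. Protocol 5.4.2 says the case is then "considered dropped out. If the emergency unblinding happens during the treatment period, the medication should be stopped". SAP 2.6 agrees: "Once the blind was broken emergently, the case was treated as a dropout". SAP 4.3.1 provides for a Day-90 mRS that is missing after unblinding and assigns its handling by the reason recorded in the CRF.

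An exit visit is requested. Protocol 5.7.2 asks the investigator to try to "complete the assessment items that can be completed at visit 4 (withdrawal visit"), whereas 6.3.2 says of subjects who drop out that "they should try to complete the visit (withdrawal visit) according to the requirements of visit 5".

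**The concern.** The full analysis set contains everyone randomised, and the primary endpoint is a Day-90 mRS. Where that score is missing, SAP 4.3.1 substitutes failure or the score closest to withdrawal. If follow-up ends because of adverse reactions, compliance or an investigator's judgement, the substitution happens for reasons that may depend on treatment. A patient who did not refuse further contact could often still have been measured.

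For safety, the endpoint is all AEs within 90 days (SAP 2.3). After withdrawal, a new AE enters the data only if the investigator already thinks it is related. That selects on causality within an endpoint meant to ignore causality. Protocol 7.3.2 applies a similar filter to SAEs, including deaths, learned of after a subject leaves the study.

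**Working it through.** **1. The plan's own figures.** Inputs (Protocol 8.1, SAP 2.5): 50% v 40%, two-sided alpha 0.05, power 80%, 1:1.

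n per group = [1.960 × √(2 × 0.45 × 0.55) + 0.842 × √(0.25 + 0.24)]² / 0.10² = 387.3, so 388.

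With 15% dropout: 388 / 0.85 = 456.5, so 457 per group and 914 in total. Both figures reproduce.

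**2. How many patients could be involved.** 0.15 × 914 = 137. The 20% dropout control target in Protocol 9.3.2 gives 0.20 × 914 = 183. Both counts include refusal of consent and loss to follow-up, which no rule change would recover. The documents attribute no share to the rules discussed here.

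**3. What each status leads to.**

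| Status | Follow-up in the text | Primary outcome used (SAP 4.3.1) |
|---|---|---|
| Stops drug for an AE, stays in study | To visit 5 (Protocol 6.3.3) | Measured Day-90 mRS |
| Leaves follow-up because of an AE | Best-effort exit visit; existing AEs followed | Failure (mRS above 1) |
| Withdrawn for poor compliance or other reasons | Best-effort exit visit | mRS closest to withdrawal; failure if none after start of treatment |
| Serious ineligibility | To visit 5 unless investigator and sponsor both end it | If ended, as in the row above |
| Emergency-unblinded | Not stated beyond dropout status | If Day-90 mRS is missing, by CRF reason |

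The first two rows can start from the same adverse reaction; whether the patient is labelled as withdrawn decides whether Day 90 is measured. Post-treatment mRS is scheduled only at Days 14, 30 and 90, so a carried score may come from the exit visit, Day 14 or Day 30.

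**4. Effect on power, as an extreme case.** Assume 457 per arm and code a fraction d of each arm as failures, so the rates become 0.50(1 − d) and 0.40(1 − d).

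| d | Rates | Power |
|---|---|---|
| 0 | 50.0% v 40.0% | 86.1% |
| 5% | 47.5% v 38.0% | 82.8% |
| 10% | 45.0% v 36.0% | 79.2% |
| 15% | 42.5% v 34.0% | 75.4% |

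For comparison, 388 completers per arm give 80.1%. The 15% row is a limit and not a forecast, because SAP 4.3.1 scores only some withdrawals as failures.

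**5. Effect of imbalance, as an illustration.** None of these inputs is in the documents. Assume equal true response p of 40% to 50%, failure-coded withdrawal of 5% in one arm and 6% to 10% in the other, and withdrawn patients who would have responded like the rest. The spurious difference is p × excess, from 0.40 × 0.01 = 0.4 points to 0.50 × 0.05 = 2.5 points. The two-sided rejection rate is then 5.2% to 11.8% instead of 5%. If withdrawn patients would have done worse than average, the shift is smaller. The sign depends on which arm has the excess.

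**6. Safety.** Take two patients with the same AE on Day 60, judged unrelated. One stayed in the study and the event is counted. The other was withdrawn on Day 20 and it is not, although that patient remains in the safety set denominator. The arm with more withdrawals would tend to show too few AEs.

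**The case against.** Several stronger readings are tempting, and the documents do not support them.

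- *That the Day-90 mRS is simply not sought after early stopping.* Patients who only stop study drug are followed to visit 5. Dropouts are asked for an exit visit and, under 6.3.2, one with visit 5 content, which includes mRS. What is missing is a clear requirement for contact at Day 90.
- *That emergency unblinding ends follow-up.* Protocol 5.4.2 and SAP 2.6 say dropout, not end of follow-up. Protocol 5.7.2 makes withdrawn subjects dropouts but does not say the converse. The SAP 4.3.1 provision is conditional. The status is unclear, not settled.
- *That ineligible or non-compliant patients are automatically lost.* Protocol 4.2 lets ineligible patients continue, 6.3.3 needs joint agreement, and the 5.7.1 withdrawal grounds are permissive.
- *That a particular bias follows.* It requires withdrawal or causality judgement to differ by arm. Judgement is blinded except in unblinded cases, and no difference is documented.

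It is also fair to say that SAP 4.3.1 fixes the replacement values in advance and adds best-case, worst-case and LOCF-based sensitivity analyses. These show how far the result depends on imputation. They recover no data, and each best- or worst-case assumption is applied alike to both arms.

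Finally, the third IDMC minutes report that all 914 patients had finished follow-up and that database lock was agreed. An amendment can no longer help this trial. The statement does not show that every Day-90 mRS exists, because under 6.3.3 a withdrawn patient's follow-up finishes at the last evaluation.

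**Conclusion.** The concern holds in limited form. For withdrawn patients the plan ends routine collection before Day 90, keeps new AEs only when judged related, leaves unblinded patients' follow-up undefined, and contradicts itself on the exit visit. The missingness is avoidable where the investigator, the sponsor or the protocol ends follow-up; it is not avoidable where the patient refuses or cannot be found.

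The planned number affected is at most some part of the roughly 137 allowed for. Between complete Day-90 data and the extreme of all 15% coded as failures, power runs from 86.1% to 75.4% at the design rates; the real loss cannot be placed within that range. The direction of any bias, in efficacy or safety, cannot be determined from the documents. This should be corrected, but it does not show that the trial's result is wrong.

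**What to change.** In Protocol 5.4.2, 5.7.1, 5.7.2, 6.3.2 and 6.3.3 and in SAP 2.6:

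- State that only a patient's withdrawal of consent to follow-up, or true loss to follow-up, ends data collection.
- Keep all other withdrawn, ineligible or unblinded patients in follow-up for vital status, all AEs and SAEs to Day 90, and the Day-90 mRS, by remote contact if needed. SAP 4.3.1 already accepts remotely obtained mRS scores during the pandemic as valid.
- Remove dropout status as a data rule for unblinded cases, leaving every medication rule as it is.
- Reconcile 5.7.2 and 6.3.2 into one exit visit that is additional to the Day-90 contact.

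The cost is a short amendment and some extra Day-90 calls.

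Since follow-up is reported complete, the equivalent for this trial is disclosure: tabulate withdrawals and emergency unblindings by arm, reason and availability of a Day-90 mRS, and state where AE collection stopped for withdrawn patients. This uses data that should already be in the database.

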#### **5.7.2. Handling of discontinuation of or withdrawal from the treatment**

Subjects who have withdrawn during the trial are all considered as dropout cases, and the reasons are shown in Section 5.7.1 "Reasons for withdrawal".

When a subject drops out, the investigator should contact the subject as much as possible to complete the assessment items that can be completed at visit 4 (withdrawal visit). If the subject drops out during the treatment period, the time of the last medication should be recorded. Those who drop out due to adverse reactions also need to be treated as specified in Section 7.3.

#### **5.7.3. Criteria for early discontinuation**

The study may be early discontinued at any time with the consent of the investigator and Sponsor, in the best interests of the subject and for reasonable medical or ethical reasons. During the discontinuation of the study, the Sponsor, the contract study organization, and the investigators will ensure that the interests of the subjects are fully considered.

The following is the criteria for early discontinuation of study:

1. The drug regulatory authority, the Ethics Committee, the Sponsor, or investigators believe that the study drug has major safety risks;
2. Major defects are found in the study protocol, or major deviations or human errors are found during the implementation of the study, which seriously affect the quality of the study and make it difficult to achieve the study objective;
3. The Sponsor may discontinue the study for any scientific, medical or ethical reasons, provided that the rights, safety, and health of the enrolled subjects are fully considered;
4. Other reasons that the Sponsor or the investigator consider as unsuitable for

continuing the study.

## **5.8. Previous/concomitant medication and therapy**

### **5.8.1. Allowed concomitant medication/therapy**

Study period refers to the period from the time of signing the informed consent form to Day 90 of medication or the last follow-up.

During the study period, therapeutic drugs excluding neuroprotective agents recommended in the *Chinese Guidelines for Diagnosis and Treatment of Acute Ischemic Stroke* 2018 and the *Chinese Guidelines for Secondary Prevention of Ischemic Stroke and Transient Ischemic Attack* 2014 are allowed to be used:

(I) General treatment and supportive drugs: antipyretics, dehydrating agents, hypotensors, lipid lowering, glucose lowering, nutritional support, antibiotic treatment. Mannitol is used as dehydrating agent only to reduce intracranial pressure due to its effect in free radical scavenging.

(II) Drugs for improving cerebral circulation:

(1) Antiplatelet drugs: including Aspirin, Clopidogrel, Dipyridamole;

(2) Anticoagulant drugs: including unfractionated heparin, low-molecular-weight heparin, heparinoids, oral anticoagulants (such as Warfarin) and thrombin inhibitors (such as Argatroban);

(3) Defibrinogen drug: including defibrase, batroxobin, ancrod, lumbrokinase, acutobin;

(4) Volume expansion drug: crystalloid fluids (such as glucose, sodium chloride injection, etc.), blood products (such as whole blood, plasma, albumin, etc.), artificial colloid fluids (such as gelatin, dextran, succinic acid gelatin, etc.).

(III) The subjects with underlying medical conditions that require long-term medication may continue to take it during the study period.

(IV) If the subject has adverse reactions, the investigator shall decide whether to use symptomatic drugs.

(V) Considering the treatment needs of the placebo group, it is allowed to use Shuxuetong injection and ligustrazine injection without neuroprotective mechanism for indications of cerebral infarction, and other drugs not for cerebral infarction or related

indications as mentioned in their package inserts.

(VI) Appropriate rehabilitation treatment shall be selected according to the *Chinese Guidelines for Diagnosis and Treatment of Acute Ischemic Stroke* 2018

All drugs used at the same time should be recorded and explained in detail on the CRFs.

### **5.8.2. Prohibited concomitant medication/therapy**

The following treatment is prohibited during the study:

Concomitant medication of following drugs should be avoided during the study:

- 1) Drugs with indications of neuroprotective agents as mentioned in their package inserts or those with similar mechanism of action, including commercially available edaravone, edaravone dexborneol concentrated solution for injection, nimodipine, gangliosides, citicoline, piracetam, oxiracetam, butylphthalide, human urinary kallidinogenase (kallikrein), cinepazide, mouse nerve growth factor, possible neuroprotective cerebrolysin (cerebroprotein hydrolysate), deproteinised calf blood serum injection, and deproteinised calf blood extractive injection. It is also prohibited to use mannitol for the purpose of neuroprotection rather than reducing intracranial pressure.
- 2) Drugs with indication of cerebral infarction as mentioned in their package inserts: Breviscapine Injection, Astragali Injection, Danshen Injection, Compound Danshen Injection, Sodium Aescinate for Injection, Puerarin Injection, Angelica Injection, Compound Angelica Injection, Safflower Injection, Ginkgo Leaf Extract and Dipyridamole Injection, Extract Of Ginkgo Biloba Leaves Injection, Ciwujia Injection, Kudiezi Injection, Xingnaojing Injection, Xuesaitong Injection/Tablet/Capsule, Xueshuantong Injection, Mailuoning Injection, Compound Musk Injection, Naoxuetong Oral Liquid/Granule, Naoxuekang Tablet/Granule/Capsule/Oral Liquid, Naoluotong Capsule, Yimaikang Tablet/Capsule, Naoxintong Tablet/Capsule, Dahuoluo Pill, Xiaohuoluo Pill, Sanfeng Huoluo Pills, Huatuo Zaizao Pill, Xinnaoshutong Tablet/Capsule, Thrombolytic Capsule, Xiaoshuan Tongluo Tablet, Vinpocetine, etc.

- 3) It's forbidden to use unmarketed drugs or other drugs for clinical trials during the study.
- 4) Drugs under post-marketing investigation with neuroprotection as the main evaluation index.

The administration of all drugs during the study should be recorded.

